**Fig 1 pone.0281991.g001:**
[figure not shown]
Parameters used to calculate the sample size based on a power analysis.

The calculation for the transmission stage was based on the same parameters. However, as this stage will be conducted in transmission chains of four people each, we divided the total number of 327 people by 4 and rounded the result to the nearest whole number, arriving at a total of 21 chains per text used and 336 participants (an increase of 9 people from the calculated sample).

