### Sample size

Individuals aged 18 years and older with access to the Internet will be selected to participate in the research. The recruitment of volunteers will be carried out through the dissemination of the survey on social networks such as Instagram, Twitter, Facebook, WhatsApp, and E-mail. To determine the sample size for the recall stage, we used the G*Power 3.1.9.7 software [25]. We conducted an *a priori* analysis to determine both the sample size and its power. As a basis for the study, we took the effect size (Odds ratio = 1.81) in a study by Bonin et al. [26] as it is the most recent study that brings memory-related variables and employs the same statistical test that we propose to use. We calculated a sample size of 327 people with an explanatory power of 95% and z = 1.64. The default for Pr(y = 1|x = 1)H0 in the G*Power software is 0.2 (i.e., a 20% probability of the event occurring if the null hypothesis is true). However, we use 0.1 to obtain an even more reliable sample size for the phenomenon we are investigating. We consider an α of 0.05, a Power (1-β err prob) of 0.95, R^2^; = 0, and normal distribution. Fig 1 presents the parameters used for this calculation.

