### Transmission stage

The second experiment to be carried out aims to test the hypothesis referring to the transmission of information related to COVID-19: specifically, on whether the presence of a prestigious role model favors the transmission of information over successive generations. Similar to the first experiment, this one will be carried out online, through a platform specifically developed for research of this nature, by the Laboratory of Ecology and Evolution of Socioecological Systems at the Federal University of Pernambuco.

A linear transmission chain experiment will be carried out, a method originally developed by Bartlett [29], which has been used in studies of cultural evolution over the years. It allows for the simulation of information transmission along a chain of individuals and occurs as follows: the first participant in the chain reads the material and, after a distraction task, is asked to recall the material read. In the original method, the resulting recall is then passed to the second participant, who does the same, and this continues along the chain (Fig 3). We will test 16 chains of four participants (representing four generations) for each proposed condition, totaling 64 chains.

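### The transmission stage reuses the recall-stage sample size, regrouped into chains of four with no allowance for dependence within chains, so the inherited 95% power does not hold for Hypothesis 1

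*Protocol article*

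**What the plan says.** The Sample size section of the protocol article derives the recall-stage number from a logistic-regression calculation in G*Power. For the effect, "we took the effect size (Odds ratio = 1.81", taken from a published memory study. For the base probability, "However, we use 0.1 to obtain an even more reliable sample size". For the error rates, "We consider an α of 0.05, a Power (1-β err prob) of 0.95". The result: "We calculated a sample size of 327 people with an explanatory power of 95% and z = 1.64".

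The text after Fig 1 then turns to the transmission stage: "The calculation for the transmission stage was based on the same parameters". Because chains have four people, "we divided the total number of 327 people by 4 and rounded the result to the nearest whole number". The outcome is reported as 21 chains for each text, or 336 people, which is 9 more than the 327. No ICC, design effect or other allowance for chains appears.

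The Transmission stage section describes the chain: "In the original method, the resulting recall is then passed to the second participant, who does the same, and this continues along the chain". The plan follows this: the corrected recall of one participant becomes the reading material of the next, through four generations, and chains are allotted to conditions. The same section plans 16 chains per condition (64 in all), and the Abstract gives eight chains per story. Under Data analysis, the model has a random effect for participant only.

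**The concern.** A sample size for independent people can be moved to a clustered design only after inflation for the correlation within clusters. Dividing by the cluster size tells the planners how many clusters hold the same number of people. It does not adjust for what those people contribute.

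Here the dependence is built into the design. Role model is constant within a chain, only the first person reads the written text, and a proposition that one person drops is generally unavailable to those who follow. For comparing role models, 336 chained people carry less information than 336 independent people. The 9 additional people come from rounding up to whole chains per text.

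What is at stake is the power claim for Hypothesis 1, which is tested in this stage, and with it how the transmission result can be interpreted.

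**Working it through.** **Inputs (Sample size section):** odds ratio 1.81, base probability 0.1, α 0.05 with z = 1.64 (hence one-sided), power 0.95, R² = 0, normally distributed predictor. Chain length is 4 and there are 4 texts. The ICC is not given and is assumed to lie between 0.05 and 0.5.

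**1. Reproduce 327.** For a Wald test of one standard-normal predictor, with variance V₀ under the null and V₁ under the alternative:

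n = (z₀.₉₅√V₀ + z₀.₉₅√V₁)² / (ln OR)²

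With V₀ = 10.016, V₁ = 11.221 and ln 1.81 = 0.5933:

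n = [1.645 × (3.165 + 3.350)]² / 0.3520 = 326.2, rounded up to 327. The printed figure reproduces.

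**2. Reproduce 336.** 327/(4 × 4) = 20.4, rounded up to 21 chains per text. Then 21 × 4 = 84 chains and 84 × 4 = 336 people. This is the independent-person number rounded up to whole chains.

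**3. What the 9 extra people cover.** With design effect 1 + (4 − 1) × ICC, setting 336/(1 + 3·ICC) = 327 gives ICC = (336/327 − 1)/3 = 0.009.

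**4. Power at 336 people on the plan's formula.** Power = Φ[(√n_eff × 0.5933 − 1.645 × 3.165)/3.350], with n_eff = 336/(1 + 3·ICC):

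| ICC (assumed) | Design effect | Effective n | Power |
|---|---|---|---|
| 0 | 1.00 | 336 | 95.5% |
| 0.05 | 1.15 | 292 | 93.0% |
| 0.1 | 1.30 | 258 | 90.2% |
| 0.2 | 1.60 | 210 | 84.4% |
| 0.3 | 1.90 | 177 | 78.9% |
| 0.5 | 2.50 | 134 | 69.1% |

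If the correlation instead decays along the chain, from 0.3, 0.5 or 0.7 between neighbours, power is 85.3%, 76.0% or 66.2%.

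**5. The other chain counts.** 16 per condition is 64 × 4 = 256 people. Eight per story is 32 × 4 = 128 people. On the same formula these give 90.0% and 67.4% even at ICC 0, and 82.4% and 58.1% at ICC 0.1.

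**6. Seven propositions per person.** The formula treats each person as one yes/no outcome, whereas the planned analysis has 336 × 7 = 2,352. A simulation was therefore run on these assumed settings: 21 chains per text, lost propositions stay lost, participant SD 1 on the logit scale, odds ratio 1.81 per step, baseline retention logits from 0 to 2, and influencer against the other three texts pooled. Tested one-sided at chain level, power was roughly 81–87%, against 91–97% if people were independent. A person-level test that ignores chains, used as a stand-in for a participant-only model, rejected a true null about 10–20% of the time at nominal 5%.

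**The case against.** Several points on the other side carry weight.

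- **No ICC is given, so the size of the shortfall is unknown.** This stands, and the figures are a range under assumption. The direction does not depend on the value, and an ICC above about 0.009 is enough to take power below 95%.
- **Seven propositions per person add information that the formula ignores.** This also stands. The plan takes no credit for them, however, so they cannot justify an unadjusted 95%.
- **A reader might infer power as low as 63–71%.** If a lost proposition stays lost, with an assumed retention of 0.5 to 0.9 per generation, the design effect for a single proposition is about 2.4 to 3.0. Applying it to 336 people yields that range. The documents do not support it as the study's power: it treats each person as giving one outcome, and it holds the odds ratio fixed when a per-generation advantage would compound along the chain.
- **A reader might also infer that the planned analysis would easily miss a true effect, and that a null would be taken as evidence against prestige bias.** The power loss belongs to an analysis that respects chains. The Data analysis section plans a participant-only random effect, and its main risk is false positives. The article does not say how a null would be read.
- **No power is printed for the transmission stage.** The 95% is inherited through the statement that the same parameters were used. That is a fair reading, but it is an inference.

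**Conclusion.** The point holds. The transmission stage is sized as if chained people were independent, and on the plan's own formula 95% power survives only at an ICC of about 0.009 or less. For 336 people, power is about 93% to 69% over an assumed ICC of 0.05 to 0.5. With seven propositions and carry-forward of losses it is roughly 81–87% at chain level, also on assumed settings.

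The formula-based figures accept the plan's one-sided test and single normal predictor, although the analysis uses a four-level factor. They do not determine the true power; they show that the inherited figure is unsupported. All figures for 336 people also depend on 21 chains per text, which the article contradicts in two places. Moving to 256 or 128 people lowers power to 90.0% or 67.4% before any correlation is considered, so that conflict can matter as much as the ICC. The underlying fault is an unstated independence assumption; the printed 327 itself is computed correctly.

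**What to change.** 1. Reconcile the three chain counts first: 21 per text (Sample size), 16 per condition (Transmission stage) and eight per story (Abstract).
2. Replace the division by four with a chain-level calculation: either a design effect, or a simulation with four generations, carry-forward of lost propositions and seven propositions per person.
3. Restate the transmission-stage power, or the smallest detectable odds ratio, at the reconciled number of chains over a stated range of within-chain correlation. Drop the inherited 95%.
4. Add a random effect for chain to the transmission model under Data analysis. The restated power applies only if the analysis accounts for chain.

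The cost is a short calculation, one revised paragraph and one added model term. No extra participants are needed, since the correction is to what the planned number can claim. The downside is a less favourable stated power for Hypothesis 1.

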#### Selection of the information used

Since information about COVID-19 has been in wide circulation throughout the population for almost two years, we will not use data pertaining symptoms and actual forms of prevention, as there is a risk of bias. Therefore, we will create fictitious information appropriate to the context. To select our prestigious role model, we considered the characteristics described in the scale developed by Berl et al. [21] to assess how people attribute prestige. These characteristics are based on social status and esteem, influence, and knowledge of a certain subject. As social media played an essential role in the pandemic scenario, mainly due to isolation measures [27], and personalities such as digital influencers gained a lot of notoriety, they serve as ideal examples for the prestigious role model. In this case, we consider digital influencers to be people who receive a significant amount of attention (the more followers they have, the greater their engagement and popularity) and have a prominent social status, expertise within their niche, and influence beyond that niche.

For the decision of the other models to be used (to be compared with the prestigious role model), we selected a role model who had knowledge on the subject of public health, but no prestige, to assess whether prestige is in fact more influential than expertise, in this scenario. For the other role models, we used a study carried out by Hornsey et al. [28], where it was stated that there are psychological roots behind our attitudes of accepting or rejecting scientific information. Six roots are then described: ideologies, vested interests, conspiracy worldviews, fears and phobias, expression of personal identity, and social identity needs. Conceptually, these roots are distinct; in practice, however, they can overlap [28]. We selected models that may have behaviors and attitudes that reflect the overlapping of these roots, such as politicians, who share the same ideologies and interests; family members, who, along with previous roots, also have the same worldviews, while also possibly validating opinions related to personal fears and phobias.

Furthermore, empirical studies have shown how politicians’ opinions are taken into account in decision-making during a pandemic [7]. Recent studies also reveal that family care is a human priority [10], so it is quite plausible for people within the family to act as role models.

We will ensure that the selected models do not contrast with the ideologies of each participant, they are unnamed, and they are in line with the political positions and personal tastes of each reader, which is clear in the texts (Table 1).

**Table 1 pone.0281991.t001:** Models used in the elaboration of the text to carry out the recall experiments and transmission of information about COVID-19.

Role Models	
Prestigious	Digital influencer with many followers and considerable influence that the participant follows and admires
Political	Politician
Experience/Knowledge	Physician
Parental	Family member (one who is closest to the participant)

### Elaboration of the texts

The texts will contain a brief contextualization of the pandemic scenario; then, a particular opinion about the use of the drug Postex in the treatment of COVID-19 will be reported and attributed to one of the role models. By attributing the opinion to the role models, we will describe the characteristics that may confer prestige onto them. In this way, we will be able to determine whether the prestigious role model influences the retention and transmission of information. The stories have approximately the same number of words, ranging from 123 to 129 (S1 File).

All texts have the same structure; first, the pandemic context; next, a model with an opinion on the use of the medication. The number of central propositions referring to each of the models is also equal (Table 2).

**Table 2 pone.0281991.t002:** Central propositions used in the story texts for the experiments on recall and transmission of information about COVID-19.

Central Propositions	
Contextualization	Pandemic context
Proposition 1	Characterization of the role model
Proposition 2	Support for use of the drug
Proposition 3	Decrease in the number of deaths
Proposition 4	Decrease in the number of hospitalizations
Proposition 5	Assertion that use is safe
Proposition 6	Success rates exceed failure rates
Proposition 7	Postex should be used

All texts will be randomized so that they have the same chance of being assigned to participants.

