## Hypotheses

**Hypothesis 1**: The transmission of information related to COVID-19 is strongly influenced by a source who possesses prestige.

*Prediction*: Information related to COVID-19 that is attributed to someone with prestige (digital influencers) is transmitted more often than the same information attributed to political role models, role models with public health expertise, and family members.

According to Henrich and Gil-White’s [12] theory, prestige is based on the merit that other people confer on certain individuals, which promotes greater admiration from others and a desire to be close. The "status" involved in this is proportional to the amount of attention received. Thus, as an individual receives more attention, their status will be higher [10]. The assumptions of the theory are as follows: [i] qualified individuals have a higher status; [ii] older individuals tend to obtain more prestige than younger individuals; [iii] individuals with perceived skill/knowledge receive privileges and are exempted from certain social obligations; [iv] people preferentially mirror qualified/successful individuals; [v] prestigious individuals are influential even beyond their domain of expertise; and [vi] prestigious individuals are more memorable.

Jimenez and Mesoudi [13] gathered existing evidence in the literature on prestige bias and added to their initial predictions, including the following: [i] prestigious individuals tend to be successful in domains that are currently important to a social group or that were valued in the recent past; [ii] prestigious individuals only achieve social influence when their domain of prestige is currently valued by a social group; [iii] the positive association between perceived success and prestige will be greater than the positive association between actual success and prestige; [iv] a more positive correlation between prestige and success indicates that more people will employ social learning with prestige bias; [v] prestigious individuals will be mirrored more often when the variation in knowledge/skill within a group is larger; [vi] prestige bias across domains occur more often when cues are not as evident within the domain tested than when those cues are clear; [vii] prestige bias across domains occur when there are general traits, which make people successful across domains [13].

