### Project

We intend to investigate whether people remember and transmit information more often when attributed to a prestigious source, in a pandemic scenario. We will use an online platform to carry out an experimental study, without the need for follow-up. The experiment will be conducted in two distinct stages, a recall stage as well as a stage for transmitting the information, both of which will be based on a fictitious text offered to the participants. This text will contain information about the use of a drug for COVID-19. There will be four versions of the text, one for each role model to be tested. Each version will consist of the same information, but only the role model attributed to the information being transmitted will change.

Since the experiment will be carried out online, there will be no need for blinding, on the part of the researchers, in carrying out the experiment and analyzing the results. More information is provided below about the selection of information along with a detailed procedure of the experiments. All data from the survey will included as supplementary material in the final articles.

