### Data analysis

To analyze the recall and transmission of information provided by each model in the texts, we consider the central propositions recalled and transmitted by the participants in each of the conditions presented in the texts. Central propositions are the key points of information in a narrative. In our texts, there are seven propositions for each model presented in each of the stories.

Each proposition was identified by its central subject (Table 2), which enabled the identification of the central propositions that were most commonly remembered by the volunteers and the models to which they belonged.

To determine which information is most likely to be remembered and transmitted, we will consider each proposition as a binary result (whether the participant remembered it or not). We will then perform a multilevel logistic regression, considering the participant as a random effect and as a fixed effect: Hypotheses 1 and 2—type of model (digital influencer, physician, politician, and family member). To test the validity of the statistical models, they will be compared with a null model (which will only consider the effect of grouping by participants using the X^2^; test for model adjustments, through the ANOVA function, and the maximum likelihood estimate. The tests will be performed in an R environment [32] using the package lme4 [33].

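### The description of the role model is itself scored as one of the seven pooled propositions, so a role-model effect, or its absence, cannot be attributed to recall or transmission of the COVID-19 information

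*Protocol article*

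**What the plan says.** **Manipulation.** The Project section says of the four texts: "Each version will consist of the same information, but only the role model attributed to the information being transmitted will change". Elaboration of the texts adds: "By attributing the opinion to the role models, we will describe the characteristics that may confer prestige onto them". Table 1 lists the prestigious model as "Digital influencer with many followers and considerable influence that the participant follows and admires"; the other three are a politician, a physician and the closest family member.

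**Question.** Under Hypotheses, the prediction is that information attributed to an influencer "is transmitted more often than the same information attributed to political role models", and likewise for the expert and family models. The prediction under Hypothesis 2 makes the same comparison. Both concern information related to COVID-19.

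**Scoring and model.** Table 2 gives an unnumbered line for the pandemic context and then seven numbered propositions. Proposition 1 is "Characterization of the role model"; Propositions 2-7 are the claims about the drug. Data analysis says "In our texts, there are seven propositions for each model presented in each of the stories" and "we will consider each proposition as a binary result (whether the participant remembered it or not"). It continues: "We will then perform a multilevel logistic regression, considering the participant as a random effect and as a fixed effect" the type of role model. The comparison model contains only the grouping by participant.

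**The concern.** Propositions 2-7 are what every reader receives in common. Proposition 1 carries the experimental manipulation, yet it counts towards the outcome on the same footing as the other six. If one source description is recalled more often than another, the pooled recall rate differs between arms even when the drug information is remembered equally well. The reverse can also happen: a poorly recalled description can offset a real advantage on the drug information.

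What is at stake is attribution. The planned test answers whether the seven-item total differs by arm. The hypotheses ask whether the shared information is better remembered or passed on because of its source.

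**Working it through.** **1. Which items differ by design.** Proposition 1 differs between arms. Propositions 2-7 (support for the drug, fewer deaths, fewer hospitalizations, safety, success exceeding failure, recommendation to use) are meant to be identical. The fixed part of the planned model has only the type of role model, so nothing in it separates Proposition 1 from the rest.

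**2. The plan's sample size.** Wald test for logistic regression with a standard normal covariate: n = (z_α√v0 + z_β√v1)² / (ln OR)², where v0 and v1 are the variance factors under the null and the alternative. Inputs from Sample size: OR 1.81, base probability 0.1, R² = 0, α 0.05 with z = 1.64 (one-sided), power 0.95. Result 326.2, rounded up to 327, which matches the article. This figure is not in dispute; it only fixes the arm size: 327/4 = 81.75, taken as 82.

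**3. Shift in the pooled rate.** If the arms differ by d in Proposition 1 and by δ in each of Propositions 2-7, the pooled rate differs by (6δ + d)/7. With δ = 0 and recall of 0.4 for Propositions 2-7 (assumed):
- d = 0.2 (0.6 vs 0.4): 3.0/7 = 0.429 vs 0.400, OR 1.13
- d = 0.3 (0.8 vs 0.5): 3.2/7 = 0.457 vs 2.9/7 = 0.414, OR 1.19
- d = 0.4 (0.8 vs 0.4): 3.2/7 = 0.457 vs 0.400, OR 1.26
- d = 0.5 (0.9 vs 0.4): 3.3/7 = 0.471 vs 0.400, OR 1.34

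Masking follows from the same formula. The pooled difference is zero when d = −6δ, so a 30-point deficit on Proposition 1 cancels a 0.30/6 = 5-point advantage on every one of Propositions 2-7.

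**4. Effect on the planned test.** Simulation of the recall stage: random-intercept logistic model, 3-df likelihood-ratio test against the null model, 82 per arm, δ = 0, the influencer arm differing from the other three in Proposition 1 only. Assumed participant variation: logit SD 0.5 to 1.0, or ICC 0.1 to 0.2. The runs number 150 to 400 per scenario, so Monte Carlo error near 5% is √(0.0475/400) to √(0.0475/150), i.e. 1.1 to 1.8 points.

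| Gap in Proposition 1 | Seven-item rejection |
|---|---|
| none | 5-8% |
| 10 points (0.5 vs 0.4) | 7-8% |
| 20 points (0.6 vs 0.4, 0.7 vs 0.5) | 5-12% |
| 30 points (0.8 vs 0.5) | 16-21% |
| 40 points (0.8 vs 0.4) | 21-38% |
| 50 points (0.9 vs 0.4) | 47-56% |

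Restricted to Propositions 2-7, rejection was 4-7% wherever it was computed. The simulated pooled odds ratios fall slightly below those in step 3 (1.10-1.11 for 20 points, 1.22-1.24 for 40), because the recall rates were set for a participant with average memory.

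**5. Does the missing proposition term matter by itself?** With item recall ranging from 15% to 80%, no arm difference and no proposition term, rejection was 5.5% at ICC 0.1 and 3.5% at ICC 0.2. Everyone is scored on all seven items, so item difficulty is balanced across arms.

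The transmission stage uses the same scoring, but the chains were not simulated. The rejection rates above apply to the recall stage only.

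**The case against.** **The texts are matched.** The article reports 123 to 129 words per text, one structure and equal numbers of propositions. That limits gross differences, but it does not equalize the content of Proposition 1, which is meant to differ.

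**Length of the description.** A reader might infer from Table 1 that a long influencer description is set against one-word labels, and that length drives the effect. The documents do not support this. Table 1 names the models and is not the story wording; the supplementary texts are not shown. The article also says that agreement with the reader's political position and tastes is made clear in the texts, and that propositions are identified by central subject. Scoring by subject would weaken any effect of length.

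**Prestigious people are more memorable.** The article lists this among the theory's assumptions, so counting the source could be deliberate, and the seven-item test is valid for the outcome it defines. That much stands. It does not justify pooling, because both predictions concern COVID-19 information; memory for the source is a separate question.

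**No proposition term.** A reader might infer that its absence creates a false role-model effect, or that adding it would cure the problem. Neither holds. Step 5 shows about nominal rejection without it, and the difficulty with Proposition 1 is a proposition-by-arm difference, which a main effect leaves in place.

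**An analysis plan may deal with it.** The item set and the fixed effect are stated choices in the article, not details left open.

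**Conclusion.** The point holds as a mismatch between outcome and hypothesis. Proposition 1 is part of the manipulation and part of the outcome, and the stated analysis cannot separate it from recall of the shared information.

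The size cannot be fixed from the documents. It depends on how differently the four descriptions are recalled, and it rests on the assumed 40% recall of Propositions 2-7 and the assumed participant variation. Gaps of 10 to 20 points matter little; gaps of 30 points or more could produce a significant result fairly often with no difference in the drug information. The direction is also open.

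It would go too far to read this as showing that the planned test has an inflated error rate as such. In the scenarios with a gap, the seven-item null hypothesis is in fact false. What fails is the attribution of the result to the COVID-19 information.

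**What to change.** State before analysis that the primary outcome for both hypotheses is Propositions 2-7, the six items common to all texts. Report Proposition 1 separately, by arm, as memory for the source. The seven-item result may be kept as a secondary analysis. A proposition fixed effect is optional, for describing which propositions are recalled most; it is not the remedy.

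No new data are needed, since each proposition is already coded individually. The loss of precision is small. With between-item correlation ρ, the variance of a participant's mean is proportional to (1 + (k − 1)ρ)/k. For ρ = 0.1 this is 1.5/6 = 0.250 with six items against 1.6/7 = 0.229 with seven; for ρ = 0.2 it is 2.0/6 = 0.333 against 2.2/7 = 0.314. Standard errors rise by about 3-5%.
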